**Primary endpoints**
California verbal learning test • “Total trials 1–5” • “Short delay” • “Long delay”
**Secondary endpoints**
Neuropsychological endpoints:
Attention
• Wechsler Adult Intelligence Scale (WAISIV) – Subtest Digit Symbol Coding
• Trail Making Test A
Memory:
• Wechsler Memory Scale (WMS-IV)
• Wechsler Adult Intelligence Scale (WAIS-IV) - Subtest Logical Memory I & II, Digit Span
Executive function:
• “Regensburger” Wortflüssigkeits-Test (RWT)
• Trail Making Test B/A
• Wechsler Adult Intelligence Scale (WAIS-IV) - Subtest Digit Span backwards
Visual construction:
• Wechsler Adult Intelligence Scale (WAIS-IV) - Subtest Block Design
Cerebral imaging endpoints
• MRI and multiparametric automated volumetric analysis by FreeSurfer with respect volumes, cortical surface deformation, segmentation of the white matter and deep gray matter structures, as well as the shift in tissue intensity
Laboratory endpoints
Pro- and anti-inflammatory biomarker • Tumor necrosis factor alpha (TNF-α) • Interleukin1 alpha,−1 beta,−6,−10 (IL-1α, IL-1β, IL-6, IL-10) • C-reactive protein (CRP) • Interleukin-1 receptor antagonist, (IL-1RA)
Neurotrophic and growth factors • Brain-derived neurotrophic factor (BDNF) • Insulin like growth factor (IGF-1) • Vascular Endothelial Growth Factor (VEGF) • Matrix-metalloproteases (MMP)
Physical activity and Exercise Endpoints
• Exercise testing • Body-Mass Index (BMI) • Bio Impedance Analysis (BIA) • Hip-to-Waist ratio (HtW-R) • Global physical activity questionnaire (GPAQ)
Cardiac imaging Endpoints
• Speckle tracking strain echocardiography
Survival related Endpoints
• Disease free survival and overall survival
Patient related Endpoints
• Pittsburgh Sleep Quality Index (PSQI) • Multidimensional fatigue inventory (MFI-20) • Functional Assessment of Cancer Therapy-General (FACT-G, FACT-G/F) • Beck-Depression-Inventar (BDI-II) • State-Trait-Anxiety Inventory (STAI)

### Drop-Out Procedure

Patients can quit study participation at any time and for any reason. Except for personal reasons, participation is terminated if participants miss HIIT sessions for more than five weeks in a row. In order to collect sufficient data for statistical analysis, participants are asked to undergo all endpoint measurements at the time of study drop-out.

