## Methods

The Exercise, Cancer and Cognition (ECCO) study was designed as a randomized controlled trial to investigate the impact of a long-term physical activity program on CRCI in patients receiving adjuvant/neoadjuvant breast cancer treatment.

The ECCO study is a monocentric two-arm 1:1 randomized controlled trial (RCT), including a 12-month intervention and control group. A detailed study-flow is shown in Figure 1. The exercise interventions start within the first week of chemotherapy and last for 12 months. The study protocol was approved by the local ethics committee of Upper Austria (Austria) (1191/2018) and registered with the WHO trial register (reference number: NCT04789187). Any modifications to the protocol, which had an impact on the realization of the study, on benefits and harms of the participants, on study objectives and design, on sample size or study procedure, required a formal amendment to the Ethics Commission and had been approved. Participants are assigned to one of two groups: an exercise intervention arm (A) and control arm (B). Group A is motivated to fulfill the general physical activity recommendations (individual heart rate definition and strength training advice, home based) (69) and should perform a supervised high intensity interval training (HIIT, center based) once a week in addition to regular care. The control arm (B) receives regular care and general physical activity recommendations. Both groups will follow the same recommended physical activity guidelines, but in contrast to the intervention arm, the control group does not receive any individual heart rate suggestions and strength training material.

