• Signed informed consent prior to randomization	• Left bundle branch block
• Fluid in German	• Chemotherapy or radiation with other indications than breast cancer diagnosis
	• Current pregnancy or plans to become pregnant within the next 3 years
	• Neurodegenerative disease

All assessments are conducted at three main time points (t_0_, t_1_, t_2_) in both groups.

t_0_ (Pre): Before first chemotherapy within ± 14 days.t_1_ (interim): After 6 months ± 14 days.t_2_ (post): After 12 months ± 14 days (end of intervention).

For participants in all groups, clinical assessments during the intervention period are additionally performed at least every second month and at each clinical visit (usual care).

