### Groups and Description of Intervention

#### Exercise Intervention Arm (A)

Participants randomized to the exercise arm are motivated to fulfill the general physical activity recommendations with a defined heart rate and material for strength training (folder and exercise video). The frequency and duration of the home-based exercise depends on individual circumstances but follows general suggestions.

American College of Sports Medicine (ACSM) has recommended the following physical activity for cancer survivors (69):

Take part in regular physical activity.Avoid inactivity and return to normal daily activities as soon as possible after diagnosis.Aim to exercise at least 150 min weekly with moderate intensity.Include strength training exercises at least 2 days per week.

The advised heart rate therefore is defined by the baseline exercise testing and adjusted after 6 months if necessary.

Additionally, group A is asked to perform a supervised HIIT at the Cardiomed Linz rehabilitation center once a week.

The high intensity exercise interventions are performed on a stationary bike (ergo_bike premium 8, daum electronic gmbh, D). An experienced and accredited therapy specialist supervises and supports the exercise interventions throughout the trial.

Participants perform alternating intervals of maximal power output P_max_ (measured by the exercise test) and rest in a ratio of 1:3. The duration of the P_max_ interval is 20 and 60 s for pause.

The HIIT program is set up in two cycles; one includes an enhancement of the weekly intervals and a recovery unit (3:1) (shown in Figure 2A). This cycle is followed by a stabilization cycle (4 weeks), in which the number of intervals is kept constant (shown in Figure 2B). The next cycle starts with a higher number of intervals and is enhanced over 3 weeks, followed by a recovery unit (3:1), and continued by another stabilization cycle (4 weeks). A schematic graphic of this periodized exercise regimen is shown in Figure 2 (71). After 6 months of intervention, a re-evaluation of the patient's performance is conducted as described above. The peak load of the intervals will be adapted according to the new P_max_ if any alteration in peak performance is observed.

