### Study Endpoints

#### Primary Endpoint

The primary endpoint is the difference from baseline (t_0_) to completion of the exercise intervention (t_2_), in the California Verbal Learning Test (CVLT) mean scores and consists of the three (sub)scores “short-delay,” “long-delay” and “total-trials 1–5” of the CVLT. The CVLT is an instrument commonly used to evaluate the individual verbal learning and memory.

The test consists of two 16-word lists. The word list A is defined as the learning-list; word list B is used to interfere (interference-list). Word list A will be read aloud to the patient 5 times, then list B will read once. After that, the patients must recall as many words as possible from list A, afterwards the semantic recall follows. After 20 min, the patient is asked to recall again as many words as possible from list A, followed by a helping recall trail. For recalling, similar, semantic and phonematic distractions and categoric prototypes will be used. There are two normed settings available for baseline and t_2_.

The (sub)scores “total-trials 1–5” ascertains the learning curve for the first word list based on 5 rounds. The “short-delay” reports the delayed recall immediately after presentation and retrieval of the second word list (as interference) and without repeating the first list. The “long-delay” is testing the recall after ~20 min.

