### Biostatistical Planning and Analysis

#### Concept

The study is based on a superiority approach with a comparison of two kinds of treatment and with three equal-ranking primary endpoints.

Treatment arms:

Treatment arm A: Endurance exercise intervention → group ATreatment arm B: No endurance exercise intervention → group B

Primary endpoints:

(1): CVLT total trials 1-5 after 12 months [-](2): CVLT short delay after 12 months [-](3): CVLT long delay after 12 months [-]

The type I error will be adjusted according to Bonferroni.

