#### Per-Protocol (PP) Population

All subjects without occurrence of any drop-out situation (all valid cases) will be included in the PP population. All variables will be analyzed. The PP analysis is paramount.

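### Missing HIIT for more than five weeks ends study participation, a rule that can act only in arm A and leaves those women without the month-12 CVLT

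*Protocol article*

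**What the plan says.** **The rule.** In the Drop-Out Procedure of the protocol article, "participation is terminated if participants miss HIIT sessions for more than five weeks in a row". The sentence opens with an exception for personal reasons. That may refer to patients who leave of their own accord, or it may exempt some absences. On either reading, other women who miss the sessions are terminated. What ends is participation in the study, not just the training.

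**Whom it can reach.** Under Exercise Intervention Arm (A), "group A is asked to perform a supervised HIIT at the Cardiomed Linz rehabilitation center once a week". In Methods, "The control arm (B) receives regular care and general physical activity recommendations". Arm B has no HIIT sessions and no matching attendance rule.

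**What is measured on termination.** "participants are asked to undergo all endpoint measurements at the time of study drop-out". This is a request. Under Primary Endpoint, the CVLT has two normed settings, assigned to baseline and t2. The article does not say which is used at drop-out.

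**What the endpoint is.** Under Primary Endpoint, "The primary endpoint is the difference from baseline" to the end of the intervention. The first of the three endpoints listed under Concept is "CVLT total trials 1-5 after 12 months". Study Population and Recruitment sets t2 at 12 months with a 14-day window either side.

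**How the analyses treat drop-outs.** The per-protocol population holds only subjects with no drop-out situation, and "The PP analysis is paramount". In the ITT population, missing primary values are replaced by the worst value assessed in the study (Handling of Implausible Values and of Missing Values).

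**The concern.** Stopping an intervention and leaving a study are different events, and the article merges them. A woman in arm A who stops training, perhaps because of fatigue or toxicity, loses her month-12 test. An equally unwell woman in arm B keeps hers, because she has no sessions to miss.

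The missing values would therefore arise in one arm only and probably relate to the outcome. The Introduction itself names depression and fatigue as interacting with cognitive impairment and calls poor adherence in intervention groups a common problem. The drop-out test does not fill the gap: it may be given in the middle of chemotherapy, and it is not at 12 months.

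This is a rule about data collection. A later analysis plan cannot recover a test that was never given.

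**Working it through.** **1. The plan's own figure.** Inputs from Table 3 and the sample-size assumptions, for CVLT long delay: difference 1.65, pooled SD 2.47, one-sided type I error 0.833% (2.5%/3), power 80%.
- Normal approximation: n per group = 2 × (2.394 + 0.842)² × (2.47/1.65)² = 46.9, so 47.
- t-test: 48.4, against 48 stated. The figure is reproduced.

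**2. Power.** The 126 already allows for drop-out. At 15% loss, 126 × 0.85 = 107 remain. At 20%, 126 × 0.80 = 101 remain. Both exceed the 96 needed. t-test power for long delay, using the Table 3 SDs, is 84% and 82%. With 15% lost in B and 30% in A it is 80%. Power is not the main problem.

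**3. Bias if terminated women are excluded (the per-protocol route).** The article gives neither the share removed by this rule nor how their scores would differ, so both are assumed.
- A share q of arm A is lost and arm B is complete, with 63 randomised per arm and no true effect.
- A latent tendency to drop out has correlation r with the month-12 score, and the q with the strongest tendency are lost.
- Bias in SD units = r × φ(z)/(1 − q), where z cuts off the fraction q. SE = √(1/63 + 1/(63(1 − q))). The type I error is the chance that the one-sided t-test at 0.833% rejects when the mean is shifted by this bias.

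| q | Women lost (of 63) | φ(z)/(1 − q) | Bias, r = 0.3 | Bias, r = 0.5 | SE | Type I error, r = 0.3 to 0.5 |
|---|---|---|---|---|---|---|
| 5% | about 3 | 0.109 | 0.03 SD | 0.05 SD | 0.181 | 1.3% to 1.8% |
| 15% | about 9 | 0.274 | 0.08 SD | 0.14 SD | 0.186 | 2.5% to 4.8% |
| 20% | about 13 | 0.350 | 0.10 SD | 0.17 SD | 0.189 | 3.3% to 6.9% |

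At SD 2.47 the bias is 0.08 to 0.43 words on long delay, against a planned difference of 1.65.

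These figures are unadjusted. The planned ANCOVA adjusts for the baseline score. With an assumed correlation of 0.5 between baseline and month 12, simulation at 15–20% loss gave 0.06–0.13 SD and 2.2–5.7%.

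**4. Effect if terminated women are replaced by the worst value (the ITT route).** If the retained women in A truly differ from B by 1.65 words, and a share q of A receives a value w words below the B mean, the difference becomes 1.65 × (1 − q) − q × w. With q = 15%:
- w = 4: 1.40 − 0.60 = 0.80 words
- w = 10: 1.40 − 1.50 = −0.10 words

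Both q and w are assumptions. Arm B is again taken as complete.

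Steps 3 and 4 push the result in opposite directions.

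**The case against.** **The size is unknown.** A reader might infer that the 15–20% drop-out in the sample-size section, 19–25 women of 126, is what this rule costs, mostly in arm A. The article does not support that. The figure is all-cause drop-out over both arms, the 20% belongs to n = 134, and patients may also leave at any time for any reason. No share is given for the five-week rule. This objection stands. At 5% of arm A the distortion is small (0.03–0.05 SD, type I error 1.3–1.8%).

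**The direction is not fixed.** A reader might infer that the rule always favours exercise. That follows only where the women are excluded and would have scored lower. Worst-case replacement works the other way. The harm therefore depends partly on the choice of leading analysis. This also stands.

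**The drop-out test may be used.** A reader might infer that it serves no analysis. The article says it is made to supply data for statistical analysis, and it analyses all variables in the ITT population. Whether it may replace t2 is not stated, and an article may leave that to the full protocol. But if it does replace t2, the endpoint is mistimed in one arm. If it does not, the endpoint is missing in that arm. Neither gives a month-12 value.

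**The personal-reasons exception may spare some women.** It might, and the wording is unclear. It reduces the number affected without removing the rule.

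**Conclusion.** The design point holds: as written, the article ends follow-up for non-attendance in the only arm that has sessions to attend, and nowhere provides a month-12 CVLT afterwards. That follows from the text and needs no assumption.

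The size does need assumptions. For a loss of 5–20% in arm A, none in B, and a drop-out/outcome correlation of 0.3–0.5, the unadjusted comparison of those retained carries a bias of about 0.03–0.17 SD and a one-sided type I error of about 1.3–7% against 0.833%. Baseline adjustment would lessen this. These figures illustrate what could happen and do not predict the trial's result. Under worst-case replacement the same losses could hide a real benefit. The point concerns validity, not power. It deserves correction because the lost tests cannot be recovered.

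**What to change.** Separate stopping of training from leaving the study.
- Leave whatever the sponsor decides about HIIT after missed weeks as it is, and record the missed sessions as a protocol deviation.
- Invite every randomised woman in either arm who has not withdrawn consent to the t2 CVLT at 12 months ± 14 days.
- Keep the assessment at drop-out for those who decline further contact, and say whether and how it enters the analysis.
- State what the exception for personal reasons means.
- Use the observed t2 values in the ITT analysis in place of worst-case replacement.

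The change has its full effect only if the ITT analysis leads. A per-protocol analysis that still excludes these women would leave the bias of step 3 in place.

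The cost is protocol and consent wording, plus some t2 visits that were already planned and would otherwise not take place. The CVLT has a delay of about 20 minutes and is done at the recruiting hospital. The statement that costs are covered up to n = 134 concerns higher drop-out and should not be read as funding these visits.

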### Adverse Events Management

Neither additional nor experimental drugs are given to patients during this clinical trial. Patients in the study arm are asked to follow an individual training regimen based on the most recent health guidelines and so did not pose a health risk. The included procedures are validated and performed under the supervision of a physician.

### Data Management

Clinical research and management software (REDCAP^®^) is used to collect the data electronically. To protect the confidentiality of the participants, all required information is identified by an individual ID number. Separate electronic case report forms (eCRF) are used for baseline and follow-up of structured interviews with study participants. In case of technical failure, paper case report forms (CRF) are used. When available, values of laboratory tests and additional data are added to the electronic database. All data capture is pre-specified by the principal investigator.

### Biostatistical Planning and Analysis

#### Concept

The study is based on a superiority approach with a comparison of two kinds of treatment and with three equal-ranking primary endpoints.

Treatment arms:

Treatment arm A: Endurance exercise intervention → group ATreatment arm B: No endurance exercise intervention → group B

Primary endpoints:

(1): CVLT total trials 1-5 after 12 months [-](2): CVLT short delay after 12 months [-](3): CVLT long delay after 12 months [-]

The type I error will be adjusted according to Bonferroni.

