### Sample Size Estimations and Determination of Sample Size

The following information and assumptions are used for sample size estimations:

Use of data from the study of Andreotti et al. (72) (baseline assessments in healthy women) for group A.Postulation of a 15% change of the mean scores in group A over group B for all 3 primary endpoints (Xgroup A = 1.15 ^*^ Xgroup B).Postulation of a 7.5% change of the standard deviations in group A over group B for all 3 primary endpoints (SDgroup A = 1.075 ^*^ SDgroup B).Type I error (Bonferroni-adjusted) = 0.833% one-sided.Type II error = 20%.Independent samples *t*-test.

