#### Results of Sample Size Estimations

The result of the sample size estimation (see Table 3) is a requirement of 48 “valid cases” per group. According to previous work and our clinical expertise we calculated sample size with *n* = 126, expecting a drop out of 15%. As drop-out rates in the literature often show great variety and the applied exercise regime (even though it is highly time efficient and supervised) is rather newly tested within this group, study capacities and all arising costs will be fully covered if we see higher drop-out rates up to *n* = 134 (Assuming a drop-out rate of 20% and considering the possible need for a non-parametric test).

**Table 3 T3:** Sample size estimation.

	**Group B**	**Group A**	**Delta**	**Pooled SD**	** *n* **
CVLT total trials 1–5 after 12 months	48.56 ± 7.47	55.84 ± 8.03	7.28	7.75	2 × 25
CVLT short delay after 12 months	11.02 ± 2.26	12.67 ± 2.43	1.65	2.35	2 × 44
CVLT long delay after 12 months	10.97 ± 2.38	12.62 ± 2.56	1.65	2.47	2 × 48

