### Statistical Methods

#### Group Comparisons of Primary Endpoints/Hypotheses Testing

If the hypothesis of normal distribution cannot be rejected (Kolmogorov-Smirnov with Lilliefors significance correction, type I error = 10%) and if homoscedasticity exists (Levene's test; type I error = 5%) a parametric analysis of covariance (ANCOVA) will be applied (type I error = 0.833% one-sided). Otherwise, a non-parametric analysis of covariance (rank analysis of covariance according to Quade) will be used (type I error = 0.833% one-sided).

Covariates are

CVLT total trials 1–5/CVLT short delay/CVLT long delay (corresponding variable) at baseline [-]BMI at baseline [kg/m^2^]Age at baseline [years]BDI II at baseline [-]STAI at baseline [-]Fatigue at baseline [yes/no]

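### The fixed 0.833% Bonferroni level for all three primary endpoints is valid, but Holm would give more power within the same 2.5% one-sided familywise error

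*Protocol article*

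**What the plan says.** The Concept section describes a superiority trial "with three equal-ranking primary endpoints" (CVLT total trials 1–5, short delay and long delay at 12 months) and then states: "The type I error will be adjusted according to Bonferroni".

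The level recurs in two places. The sample size assumptions give "Type I error (Bonferroni-adjusted) = 0.833% one-sided" with "Type II error = 20" percent. In the paragraph on hypothesis testing, "a parametric analysis of covariance (ANCOVA) will be applied (type I error = 0.833% one-sided"), and the same level is given for the rank-based alternative according to Quade. No step-down or other sequential rule appears.

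The sample size section assumes a benefit on every endpoint: "Postulation of a 15% change of the mean scores in group A over group B for all 3 primary endpoints". Table 3 then asks for 2 × 25, 2 × 44 and 2 × 48 valid cases, so long delay sets the trial size. Planned enrolment is 126, with 15% drop-out expected.

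**The concern.** With three hypotheses of equal rank, each endpoint's own result matters. A fixed 0.833% for each ignores what is learned from the others. Once one null hypothesis has been rejected, at most two can still be true, and the full three-way correction is stricter than the familywise bound requires.

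Table 3 suggests the difference could be material. Total trials needs about half the patients of the other two scores. In a trial sized for long delay it will almost always be rejected if the assumptions hold, and a step-down rule would then test the two recall scores at a less strict level. What is at stake is power for short and long delay, at no extra patients. The validity of the trial is not in question.

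**Working it through.** **Inputs.** Table 3 gives difference and pooled SD per endpoint: total trials 7.28 and 7.75 ("48.56 ± 7.47 55.84 ± 8.03 7.28 7.75 2 × 25"), short delay 1.65 and 2.35 ("11.02 ± 2.26 12.67 ± 2.43 1.65 2.35 2 × 44"), long delay 1.65 and 2.47. Standardised effects d = difference/SD:
- total trials 7.28/7.75 = 0.939
- short delay 1.65/2.35 = 0.702
- long delay 1.65/2.47 = 0.668

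Level per test 2.5%/3 = 0.833% one-sided; power 80%. The protocol gives no correlation between the endpoints and none between baseline and outcome, so both are assumed below.

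**Step 1: reproduce the stated sample sizes.** Normal approximation, n per group = 2(z₁₋α + z₁₋β)²/d², with z = 2.394 and 0.842:
- total trials 20.94/0.939² = 23.7, so 24
- short delay 20.94/0.702² = 42.5, so 43
- long delay 20.94/0.668² = 46.9, so 47

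The noncentral t distribution gives 26, 44 and 49. The plan's 25, 44 and 48 lie within 2 of either set, so its figures are reproduced. Long-delay power at 48 per group is 79.6%.

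**Step 2: the Holm rule.** Order the three p-values. Test the smallest at 0.833%, then the next at 1.25%, then the largest at 2.5%, stopping at the first failure. The first step is the Bonferroni test, so the chance of at least one rejection is identical. Later steps use higher levels, so nothing that Bonferroni rejects is lost.

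**Step 3: limits for long delay at 48 per group.** A t-test at a fixed 0.833%, 1.25% or 2.5% has power 79.6%, 83.8% or 90.0%. Holm must lie between the first and the last. Total trials has power 98.4% at 0.833%, so the later steps are nearly always reached. Simulating correlated t statistics gives 88% for long delay (87.6% to 89.1% for endpoint correlations from 0.9 down to 0), against 80% for Bonferroni. Short delay goes from 84% to between 89% and 92%.

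**Step 4: the trial as planned.** Enrolment of 126 with 15% drop-out leaves 126 × 0.85 = 107.1, about 53 per arm. The primary test is an ANCOVA that includes the baseline value of the same score. With baseline-outcome correlation r, the residual SD is SD × √(1 − r²), so the noncentrality is d√(n/2)/√(1 − r²). The simulation used this with 2n − 2 degrees of freedom, ignored the other covariates and took endpoint correlation 0.7.

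| Effects | r (assumed) | Long delay, Bonferroni | Long delay, Holm | Gain (points) |
|---|---|---|---|---|
| Table 3 | 0 | 84% | 91% | 7 |
| Table 3 | 0.5 | 94% | 97% | 3.5 |
| Table 3 | 0.7 | 99.1% | 99.7% | under 1 |
| 25% smaller | 0 | 56% | 67% | 12 |
| 25% smaller | 0.5 | 70% | 81% | 10 |
| 25% smaller | 0.7 | 88% | 94% | 6 |

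Gains are taken before rounding.

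**Step 5: error control and the limiting case** (48 per group, endpoint correlation 0.7).
- All three nulls true: familywise error 1.95% under both procedures.
- Total trials and short delay improved, long delay null: false claim on long delay 0.8% with Bonferroni and 2.5% with Holm. Both are within the bound.
- Only long delay improved: power 79.7% under both, so no gain.

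**The case against.** The strongest reply is that nothing here is wrong. Bonferroni is valid, 0.833% is exactly 2.5%/3, the level is the same in all three places, and the trial was sized for its weakest endpoint at that level. This stands: the point is about efficiency and exposes no error. The plan is not underpowered on its own assumptions either. It remains worth raising because the article fixes the decision rule outright and does not leave it to a later analysis plan.

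Several stronger readings are tempting and not supported:
- **That the planned trial would gain 8 points on long delay.** That figure belongs to 48 per group and an unadjusted t-test. The protocol enrols more and adjusts for baseline, which shrinks the gain to between under 1 and 7 points with the Table 3 effects.
- **That Bonferroni buys nothing in error control.** Under partial nulls it is stricter for each single claim (0.8% against 2.5% in the case above), and simultaneous confidence limits match its decisions directly.
- **That power is lost on the scores closest to the hippocampal hypothesis.** The Introduction credits hippocampal sensitivity to the CVLT as a whole, and Concept ranks the three scores equally.
- **That a higher chance of winning on all three meets a stated goal.** The protocol sets no requirement that all three be significant.

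A positive correlation between the scores is also only an inference from their coming from one test. Holm's validity does not depend on it.

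**Conclusion.** The point holds as a modest, cheap improvement. Single-step Bonferroni is a valid choice that leaves some power unused; Holm recovers it within the same 2.5% one-sided familywise bound and keeps the endpoints equal in rank.

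The benefit is small if the Table 3 effects are real and baseline scores predict outcome well. It is most useful, at about 6 to 12 points for long delay, if the true effects are a quarter smaller than postulated. These sizes rest on the assumed endpoint correlation of 0.7, the assumed baseline correlations of 0 to 0.7, approximately normal scores and about 53 analysable patients per arm. The rank-based alternative was not simulated. The gain also requires a true effect on at least one other endpoint, as the sample size section assumes. The probability of at least one significant primary endpoint is the same under both procedures.

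**What to change.** Before outcome data are seen by arm:

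1. In Concept, replace the Bonferroni sentence with: *The familywise one-sided type I error of 2.5% is controlled by the Holm procedure across the three primary endpoints.*
2. In Group Comparisons of Primary Endpoints/Hypotheses Testing, replace the fixed 0.833%, for both the ANCOVA and the Quade test, with the Holm levels: 0.833% for the smallest p-value, 1.25% for the next, 2.5% for the largest, stopping at the first non-significant result. Holm uses only the p-values, so it works even if some endpoints are analysed parametrically and others by ranks.
3. Leave the sample size calculation at 0.833% as the conservative case.

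The cost is a few lines of text and no extra patients or visits. Simultaneous confidence limits will no longer correspond exactly to the test decisions, and per-endpoint error under partial nulls is higher, though within the bound. Because the Methods section required a formal ethics amendment for changes affecting objectives, design or procedure, a short amendment may be needed. A change made after outcomes are known by arm would look data-driven and should not be attempted.
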